# Ultrasound-Guided High-Intensity Focused Ultrasound Combined With PD-1 Blockade in Patients With Liver Metastases From Lung Cancer: Protocol for a Single-Arm Phase 2 Trial

**DOI:** 10.2196/59152

**Published:** 2024-11-29

**Keywords:** high-intensity focused ultrasound, programmed cell death protein, PD-1 blockade, liver metastases, lung cancer, immunotherapy, treatment efficacy, quality of life, HILL study

## Abstract

**Background:**

While immunotherapy has revolutionized oncological management, its efficacy in lung cancer patients with liver metastases remains limited, potentially due to the unique immunosuppressive microenvironment of the liver. Local liver treatment has been shown to enhance the immunotherapy response, and high-intensity focused ultrasound (HIFU), a minimally invasive local treatment, has demonstrated promising results in combination with immunotherapy. However, clinical data regarding HIFU in lung cancer with liver metastases are limited.

**Objective:**

We designed the HILL (Ultrasound-Guided High-Intensity Focused Ultrasound Combined With PD-1 Blockade in Patients With Liver Metastases From Lung Cancer) study to investigate the effectiveness and safety of HIFU in combination with immunotherapy for lung cancer with liver metastases.

**Methods:**

The HILL study is a single-armed, single-center, phase 2 clinical trial that will enroll 30 patients with lung cancer and liver metastases. The treatment regimen involves administering HIFU to liver metastases 1 week before the first dose of a programmed cell death protein (PD)–1 blockade, which is then administered every 3 weeks. The primary aim is to determine the overall response rate based on immune-related response criteria. Secondary aims include safety, progression-free survival, overall response, overall survival, and quality of life. Exploratory studies will also be conducted using whole blood, plasma, archival cancer tissue, and tumor biopsies during progression or relapse to identify potential biomarkers.

**Results:**

The study was funded on March 14, 2022, and received ethical approval on April 27, 2022. Clinical trial registration was completed by June 10, 2022, with participant recruitment beginning on July 10, 2022. Data collection commenced on July 14, 2022, with the enrollment of the first patient. By April 2024, 6 participants had been recruited. The results are expected to be published in December 2026.

**Conclusions:**

This study seeks to improve treatment outcomes for lung cancer patients with liver metastases by combining HIFU and PD-1 inhibition. The study also aims to identify potential biomarkers through exploratory research that can aid in selecting patients for optimized outcomes in the future.

**Trial Registration:**

Chinese Clinical Trial Registry ChiCTR2200061076; https://www.chictr.org.cn/showproj.html?proj=170967

**International Registered Report Identifier (IRRID):**

DERR1-10.2196/59152

## Introduction

Lung cancer is the second most frequently diagnosed tumor and the largest cause of cancer-related fatalities globally, accounting for roughly 1 in 10 (11.4%, 2.2 million) new cancer cases and 1 in 5 (18%, 1.8 million) deaths annually [1,2]. Immunotherapy, a landmark breakthrough in cancer treatment, has revolutionized the field of oncology, contributing to a recent accelerated decline in lung cancer mortality [3,4]. Encouraging clinical trial results with immune checkpoint blockade (ICB) have demonstrated the efficacy of this approach in lung cancer, leading the US Food and Drug Administration to approve programmed cell death protein (PD)–1 inhibitors for all stage III to stage IV lung cancers [3].

Nevertheless, a substantial proportion of patients fail to benefit from immunotherapy, particularly those with lung cancer liver metastases [5]. The existence of baseline liver metastases in patients with lung cancer has been connected with a reduced response to immunotherapy. In the Checkmate 017 and Checkmate 057 trials, the 3-year overall survival (OS) rate for subgroups of patients with lung cancer liver metastases treated with pembrolizumab was 8%, as compared to a 3-year OS of 17% across all enrolled patients [6]. Similarly, in the Keynote 001 trial among patients with non–small cell lung cancer (NSCLC), liver metastasis was linked with a decreased treatment response and shorter progression free survival (PFS) in comparison to patients without liver metastasis [7]. In patients with NSCLC with similar PD-L1 expression, tumor burden, and mutational burden, the presence of liver metastases was linked with reduced OS regardless of age, sex, or treatment modality. [8,9]. Liver metastases are independently associated with a poorer response to immunotherapy, primarily due to the liver’s unique immunosuppressive microenvironment [10]. The liver processes a vast array of harmless dietary antigens daily, necessitating a state of immune tolerance [11]. Metastatic lesions in the liver further enhance this immunosuppressive milieu. Liver metastases highly express integrin receptors, including cluster of differentiation [CD] 44 and lymphocyte function–associated antigen-1, which promotes the sequestration of activated peripheral T cells into the liver, thereby reducing T cell distribution abnormalities [12]. Additionally, liver-infiltrating myeloid cells in metastatic lesions induce T cell apoptosis via the Fas-FasL pathway, resulting in T cell depletion [13]. This extensive antigen-specific T cell exhaustion drives immunosuppression in preclinical models and cancer patients with liver metastases, leading to the enlargement of metastatic lesions and a poor response to immunotherapy [14].

Local treatment of liver metastases may be practical to counter this tumor-permissive immune microenvironment. Radiation therapy (RT) that targets the liver can both inhibit immune-suppressing myeloid cells and boost T cell immunity [13,15]. A preclinical study showed that mice treated with a combination of RT and immunotherapy demonstrated remission of both liver and subcutaneous tumors and considerably increased survival [13]. In another report, a White patient aged 64 years with chemotherapy-resistant metastatic lung adenocarcinoma who received local RT to one of the liver metastases combined with immunotherapy generated a therapeutically effective antitumor immune response [16]. Therefore, we propose that localized therapies targeting hepatic metastases, such as RT, may enhance the efficacy of ICB in patients with liver metastases.

Based on an understanding of tumor–immune system interactions, oncologists categorize tumors as “hot” (high immune cell infiltration, high immune scoring) or “cold” (low infiltration, low immune scoring) based on the type, density, and location of immune cell infiltration. This classification has been validated in patients with tumor, demonstrating its predictive value for tumor recurrence and survival outcomes [17]. In “cold” tumors, the efficacy of ICB is markedly poor, often resulting in no response or excessive adverse reactions [18]. High-intensity focused ultrasound (HIFU) can create a favorable temporal window for immunotherapy to turn previously immunologically “cold” tumors into immune-reactive “hot” tumors. HIFU uses specialized ultrasonic focusing equipment to generate focused ultrasound beams that penetrate the skin and tissue to form focal points deep within the body. At these focal points, the ultrasound intensity is extremely high, generating heat that can rapidly elevate the temperature of exposed tissues above 60°C. When this exposure lasts longer than 1 second, most cells within the tissue undergo immediate irreversible death, minimizing potential damage to surrounding nontarget tissues [19]. The thermal ablation effect of HIFU induces coagulative necrosis in tumor tissues by moving the focal point, thereby rapidly reducing tumor burden and locally releasing tumor antigens. Unlike RT, HIFU can be safely reapplied without increasing systemic toxicity risks, allowing clinicians to administer multiple local treatments even in the event of local tumor recurrence.

As a method for real-time imaging and noninvasive local thermal ablation, HIFU is being developed as an alternative to conventional oncologic therapy for a variety of solid malignant tumors, such as liver, kidney, and bone tumors [20-22]. In a rat tumor model of refractory neuroblastoma, HIFU in combination with immunotherapy significantly improved the antitumor response, increasing the survival rate from 0% to 62.5% [23]. The combination’s proposed mechanism of action is shown in Figure 1. In a syngeneic mouse model of epithelial breast cancer, Silvestrini et al [24] also found that immunotherapy combined with HIFU treatment could significantly reduce the number of macrophages and bone- and marrow-derived suppressor cells in tumor tissues, and it could promote the polarization of monocytes to the M1 type. In addition, it significantly upregulated PD-L1 in CD45+ cells and CD8+ T cells generated by IFN-γ, thereby enhancing antitumor immunity.

However, data on the combination of HIFU and immunotherapy in patients with lung cancer with liver metastases is limited. The HILL (Ultrasound-Guided High-Intensity Focused Ultrasound Combined With PD-1 Blockade in Patients With Liver Metastases From Lung Cancer) study intends to investigate the therapeutic efficacy and safety of PD-1 blockade in conjunction with HIFU.

**Figure 1 figure1:**
[figure not shown]
Hypothesis diagram of the research mechanism of HIFU enhancing immunity. HIFU, high-intensive focus ultrasound; TAAs, Tumor Associated Antigens; DAMPs, damage associated molecular patterns; APC, Antigen Presenting Cells.

## Methods

### Ethical Considerations

The trial has received ethics approval from Xiangtan Central Hospital Ethics Committee (2022-04-001). All participants provide full informed consent to participate in HILL. The data of the enrolled participants were kept strictly confidential and were anonymized for deidentification. The participants are exempted from any fees for ultrasonic monitoring. The trial is conducted in conformity with the Declaration of Helsinki and Good Clinical Practice guidelines.

### Study Design

The HILL study is a single-center, single-arm, phase 2 trial conducted with lung cancer patients with liver metastases (Chinese Clinical Trial Registry ChiCTR2200061076). Recruitment for the research began on July 10, 2022, and it is expected to be completed in June 2025.

### Eligibility Criteria

The inclusion criteria are as follows: (1) age 18-75 years; (2) histologically or cytologically confirmed NSCLC; (3) liver metastases confirmed by abdominal imaging, such as computerized tomography (CT) or magnetic resonance imaging (MRI); (4) negative for epidermal growth factor receptor and anaplastic lymphoma kinase, as assessed by polymerase chain reaction or next-generation sequencing; (5) Eastern Cooperative Oncology Group performance status 0-2; (6) at least 2 measurable lesions according to Response Evaluation Criteria in Solid Tumors 1.1 (RECIST1.1) guidelines ; (7) asymptomatic (identified as being without significant symptoms at baseline, judged by the investigator as not requiring steroids and/or local treatment) or symptomatically stable brain metastases (without significant symptoms after local treatment, such as RT, and at least 7 days free from steroids and/or anticonvulsant therapy at the time of enrollment); (8) requirement for immunotherapy; (9) liver metastases (confirmed by imaging and multidisciplinary tumor board consultation) that can be treated with HIFU; (10) agreement to use effective contraception during the beginning of the trial and 90 days after the dose; (11) written informed consent.

Exclusion criteria for patients are as follows: (1) mixed lung cancer, including neuroendocrine tumors or sarcoma; (2) history of other malignancies within 5 years; (3) effusions of the third space that cannot be drained or otherwise treated; 4) severe interstitial pneumonia or severe diffusion dysfunction; (4) liver function with Child-Pugh grade C; (5) history of immunodeficiency disease necessitating long-term treatment with glucocorticoids; (6) history of acute cardiovascular or cerebrovascular disorders, including acute cerebral infarction and acute coronary syndrome, within the last month; (7) pregnant or lactating women; (8) life expectancy 3 months or less.

### Intervention

Eligible patients will receive HIFU on liver metastases and PD-1 blockade therapy. Given the potential immunomodulation effect of HIFU, ablation of metastatic liver lesions was planned to take place within no more than 7 days of immunotherapy. The PD-1 blockade was injected repeatedly every 3 weeks for 6 cycles. The combination of immunotherapy and ablation was administered once in week 1. The study schema provides a comprehensive summary (Figure 2). Patients who are considered to have obtained clinical benefits, including a complete response (CR), partial response (PR), or having achieved stable disease (SD), will be allowed to continue PD-1–blocking medicines (every 3 weeks) for up to 2 years beyond the end of the trial. Patients with progressive disease will exit the trial or undergo re-ablation with HIFU according to their choice. Re-ablation will be performed in liver metastases without changing the immunotherapy regimen, and the efficacy will be evaluated 3 weeks later. If the treatment outcome is progressive disease, the patient will be withdrawn from the study. If the outcome is SD, PR, or CR, the patient will be treated and followed up. The standard PD-1 blockade treatment plan for advanced lung cancer with liver metastases will be used, as determined by the investigators and based on clinical guidelines.

Whole blood, plasma, archived cancer tissue, and tumor biopsies will be taken for exploratory research. Given the stability and availability of the test, peripheral blood will be obtained for lymphocyte subsets and the levels of 12 cytokines (tumor necrosis factor [TNF]-α, interleukin [IL]-6, IL-10, IL-17, interferon [IFN]-α, IL-1β, IL-2, IL-5, IL-8, IL-12P70, IFN-γ, IL-4) will be measured before and after HIFU treatment. Tumor biopsy tissue will be embedded in paraffin and analyzed for immune cell infiltration and PD-L1 expression. This information will help us determine whether the medication modifies the diversity of immune response and whether these changes are reflected in the blood. This could aid in the selection of predictive biomarkers for patients in future trials by connecting immunological alterations to clinical symptoms.

**Figure 2 figure2:**
[figure not shown]
Details of the scheduling for all planned blood sampling and tumor imaging operations during the trial to document the treatment’s safety and efficacy. Palliative radiation therapy for liver metastases and other immunotherapy treatments will not be performed. CT: computerized tomography; DCR: disease control rate; HIFU: high-intensity focused ultrasound; ORR: overall response rate; PD: programmed cell death protein; PFS: progression free survival.

### Focused Ultrasound Ablation

Patients were chosen according to the following HIFU treatment inclusion criteria: (1) suitability for anesthesia and sedation, (2) visibility in diagnostic sonography, (3) accessibility (maximum of 11 cm between the skin and the deepest tumor sections), (4) absence of extensive scarring or extensive calcifications along the acoustic route, and (5) absence of metal clips following surgery. Ultrasound-guided HIFU will be performed with a HIFU system (the Focused Ultrasound Tumor Therapeutic System [model-JC200]; Chongqing Haifu Medical Technology Co Ltd), with the patient in a lateral position. Operational details were chosen with reference to previous studies [25,26]. Prior to HIFU treatment, ultrasound localization is required to assess the safety of the patient’s acoustic channel and the accessibility of the treatment target area to determine the treatment regimen. Gastrointestinal preparation is required the day before HIFU treatment, similar to the preparation before colonoscopy. To minimize skin damage caused by HIFU, the treatment area should be shaved and moisturized on the day of surgery. The patient is given general anesthesia by a qualified anesthesiologist. During treatment, ultrasound can be used to detect the distance between the treated lesion and the edge of the lesion and the surrounding vulnerable structures (eg, the intestinal and biliary stents) in real time to prevent complications caused by heat. The power of HIFU ablation will be adjusted in real time according to the treatment.

If a patient has multiple liver metastases, HIFU ablation should not be performed on more than 3 lesions at once to ensure patient safety and tolerance. If there are more than 3 liver metastases, it is possible to ablate the largest 3 first, monitor the remaining lesions, and ablate them again if necessary.

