### End Points

Overall response rate (ORR) is the primary end point. The secondary end points are PFS, OS, disease control rate, safety, and patient-reported outcomes, including the results of the European Organization for Research and Treatment of Cancer Quality of Life Questionnaire–Core 30 and Quality of Life Questionnaire–Lung Cancer Module 13. MRI or CT examinations will be administered at the start point, week 3, and each 6 weeks following. According to the RECIST1.1 and the National Cancer Institute Common Terminology Criteria for Adverse Events (version 5.0), tumor response and adverse events will be evaluated and recorded during therapy and within 28 days after the last dose, respectively. Telephone checks will be conducted every 3 months until the end of the trial, death, or loss to follow-up.

After illness progression or withdrawal from the trial’s treatment, the use of anticancer medication will be recorded. ORR is the proportion of enrolled patients with a CR or PR based on imaging. PFS is the length of time between enrollment and the occurrence of disease progression. OS is the duration between enrollment and death.

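### The protocol gives two different triggers for further HIFU, and the looser one lets a growing liver lesion be ablated before progression is recorded, which can bias PFS

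*Protocol article*

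**What the plan says.** Two sections of the protocol article deal with HIFU after the initial treatment.

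- **Intervention.** The starting treatment is described as follows: "The combination of immunotherapy and ablation was administered once in week 1". Later ablation is tied to progression: "Patients with progressive disease will exit the trial or undergo re-ablation with HIFU according to their choice". The follow-up to that re-ablation is also given: "Re-ablation will be performed in liver metastases without changing the immunotherapy regimen, and the efficacy will be evaluated 3 weeks later".
- **Focused Ultrasound Ablation.** A limit per session comes first: "HIFU ablation should not be performed on more than 3 lesions at once to ensure patient safety and tolerance". For patients with more lesions than that, the text continues: "it is possible to ablate the largest 3 first, monitor the remaining lesions, and ablate them again if necessary". It gives no trigger, time window, limit on sessions or reference to progression.

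The End Points section defines PFS by progression only: "PFS is the length of time between enrollment and the occurrence of disease progression". The scan schedule is: "MRI or CT examinations will be administered at the start point, week 3, and each 6 weeks following". Disease control rate is listed as a secondary end point but not defined. No rule covers a liver lesion that is ablated during follow-up without recorded progression.

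**The concern.** The two sections set different conditions for the same act. Under one, further HIFU follows progression. Under the other, it follows monitoring of the untreated lesions and a judgement that it is needed. An investigator who follows the second text literally may see a leftover lesion grow, short of progression, and ablate it. That lesion can then no longer produce the progression event that defines PFS.

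The trial is open and single-arm, so the decision is made with the lesion's course in view and no control group shares the effect. The lesions concerned are also informative. The Discussion hypothesises that HIFU enhances the response to PD-1 blockade, and liver lesions not ablated in week 1 are where such an effect could be seen apart from the ablation itself.

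**Working it through.** The plan gives no figure on this point, so there is none to reproduce. The check sets the texts side by side and follows one patient through them.

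**1. The triggers**

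| Feature | Intervention | Focused Ultrasound Ablation |
|---|---|---|
| Who | Patients with progressive disease | Patients with more than 3 liver metastases |
| Trigger | Progression, then patient's choice | Need, undefined, after monitoring |
| Progression recorded first? | Yes | Not required, not excluded |
| Assessment afterwards | 3 weeks later | Not stated |

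**2. What each kind of later HIFU does to PFS as defined**

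- *After recorded progression:* the event date already exists, so this mismatch does not affect it.
- *A further session held only because of the 3-lesion limit:* the session is not selected by growth, so the selective bias described here does not arise.
- *Prompted by growth of an untreated lesion, before progression:* no event is recorded at ablation, and a later progression call on that lesion is delayed or prevented.

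Only the third kind is a problem. The text permits it but does not separate it from the second.

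**3. One hypothetical patient**

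Assume 5 liver metastases, of which 3 are ablated in week 1 and 5 − 3 = 2 remain. Weeks are counted from the start point, which is taken to coincide with enrollment. Scans fall at week 3, then 3 + 6 = 9, 9 + 6 = 15 and 15 + 6 = 21.

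- At week 9 a leftover lesion has grown, but not enough for progression. Left alone, it would meet the criteria at week 15.
- It is ablated at week 10, and nothing else progresses by week 15.
- PFS without the ablation: 15 weeks.
- PFS as defined, with the ablation: 21 weeks at the earliest on scheduled scans, a shift of at least 21 − 15 = 6 weeks, or one scan interval.
- PFS if growth-prompted ablation counts as an event: 10 weeks.

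In this example the stated definition errs late and the alternative errs early, so reporting both brackets the value.

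**4. Weight of one patient**

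If all 30 planned patients are followed to a fixed time, one patient changed from progressed to progression-free moves the proportion by 1/30 = 3.3 percentage points. This is a conversion, not an estimate. The number of such patients cannot be derived from the documents.

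**5. Disease control**

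The result depends on the missing definition. If the rate uses best response, the patient above was already stable at week 9 and counts as controlled either way. If it is read at a fixed later time, the ablation can change the answer.

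**The case against.** The strongest reply is that the two sections can be read together. The Intervention section would say when re-ablation happens, and the Focused Ultrasound Ablation section how many lesions may be treated per session. The second text follows directly on a safety limit and looks like an operating instruction. HIFU is part of the tested regimen, so a staged session may be planned treatment and not rescue. The article also condenses a longer protocol, and the schema figure, which is not shown, may define the condition. Progression outside the liver or in new lesions would still be counted.

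Much of this stands. The harmonised reading is possible, but nothing in the text requires it, and monitoring lesions before deciding on need is naturally read as acting on what is seen. The mismatch is in stated text, not in a detail left out.

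A reader might infer more than the documents support:

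- *That later HIFU contradicts the single week 1 administration.* It does not. The Intervention section itself allows later re-ablation, so that sentence describes the initial combined treatment and is not a cap.
- *That the plan provides for ablation before progression.* The wording permits it without stating it.
- *That the bias always favours the regimen.* Sessions staged only because of the 3-lesion limit are not prompted by growth.
- *That ORR is inflated.* The lesions at issue are those left after the largest 3, and the documents do not say whether they are target lesions. No effect on ORR through this route is shown.
- *That PFS or disease control shifts by 10 to 17 points.* This needs 30% to 50% of patients with more than 3 metastases and one third of those ablated early: 30 × 0.30 × 1/3 = 3 and 30 × 0.50 × 1/3 = 5, or 3/30 = 10% and 5/30 = 17%. Neither rate has a source in the documents, and the sum treats every such ablation as a progression removed or delayed.

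**Conclusion.** The concern holds in limited form. The Intervention and Focused Ultrasound Ablation sections do not agree on the trigger for further HIFU. On a literal reading, a growing untreated liver lesion can be ablated before progression is recorded, and the PFS definition has no answer to that. Where it happens, progression can be delayed or hidden and PFS biased in favour of the regimen. Disease control is exposed only under some definitions of that rate.

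The size cannot be computed from the documents. The 6-week shift in the example assumes scheduled scans only and no progression elsewhere. The point concerns secondary end points. It rests on the article's wording, which a fuller protocol may resolve.

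**What to change.** 1. Reconcile the two sections on when further ablation is allowed. No clinical rule is proposed here. The texts need to say the same thing.
2. For any HIFU after week 1 given without recorded progression, record the date and the reason: staged because of the 3-lesion limit, or prompted by lesion growth.
3. Keep the stated PFS definition for the main analysis. Add a prespecified sensitivity analysis that counts growth-prompted ablation of a lesion not treated in week 1 as a PFS event on the date of ablation. Making this the main rule for every later session would score patients staged for tolerance as having progressed.
4. Report best response and disease control also from only the scans taken before such an ablation.

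The cost is protocol wording, one extra data field and a little more analysis, with no new patients or procedures. The sensitivity results may look less favourable. By April 2024, 6 of the planned 30 participants had been recruited, which left 30 − 6 = 24 to come at that date, so most of the data could be collected under the clarified rule.
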